#### Secondary outcomes.

Secondary outcomes are divided into intraoperative and postoperative data. Intraoperative data are (1) lowest systolic BP (mmHg), (2) blood loss during surgery (ml), (3) the requirement of vasopressors (no. and %), (4) urine output (ml), (5) serum lactate level (mg/dl), (6) brain relaxation score (percentage of a four-point scale), and (7) the incidence of extubation in the operating theater (no. and %). Postoperative data will be collected at the neurosurgical ICU, including (1) the length of time the patient is mechanical ventilation dependent (hours), (2) serum blood lactate, (3) chest X-ray, and BUN/Cr values and (4) The duration of the patient’s stay in the ICU (day).

Secondary outcomes are categorized as either confirmatory or exploratory to guide interpretation. Confirmatory secondary outcomes include serum lactate levels (intraoperative and postoperative), duration of ICU stay, and lowest systolic blood pressure. These outcomes will be analyzed with adjustments for multiple comparisons using Bonferroni correction. The remaining secondary outcomes, comprising less critical intraoperative variables such as brain relaxation score or urine output and postoperative variables such as chest X-ray abnormalities, are designated as exploratory. Exploratory outcomes will be reported descriptively and analyzed for hypothesis generation, without corrections for multiple comparisons.

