### Sample size calculation

The primary outcome is the intraoperative fluid volume administered. The calculation of sample size utilized data from the research conducted by Janani Gopal et al [18]. The average fluid volume administration of patients in the CVP and PPV groups were 4,300 and 3,500 ml, respectively. In another study, the groups that used CVP guidance and those that used PPV guidance had a mean intraoperative fluid volume difference of 556 milliliters [25]. With the power of 80%, a 0.05 two-sided difference, the calculated sample size was 25 patients/group. Given a dropout rate of 5%, we will enroll 54 patients. The website clincalc.com is used to calculate the sample size. We anticipate a minimal drop-out and low loss to follow-up rate, as the study is conducted while the patient is under general anesthetic during surgery. Additionally, post-surgery, all patients will be admitted to the neurosurgical ICU, where we can gather data regarding the duration of their ICU stay.

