### Adjustments and multiple comparisons

To adjust for potential baseline covariate imbalances, specific analyses including ANCOVA, Cox proportional-hazards model, or LMM) will be used. To account for multiple comparisons across all secondary endpoints, a Bonferroni correction adjustment, will be applied.

A two-sided p-value of <0.05 will be considered statistically significant for the primary endpoint. The exploratory secondary analyses will report unadjusted p-values to guide future research. All statistical analyses will be performed using SPSS software by an expert statistician.

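### Confirmatory secondary outcomes: single-step Bonferroni is valid, but Holm's step-down version gives the same family-wise guarantee and never rejects less (optional improvement)

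*Protocol article*

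**What the plan says.** Under Outcomes, Secondary outcomes, the protocol article splits the secondary outcomes in two. The first group is defined as follows: "Confirmatory secondary outcomes include serum lactate levels (intraoperative and postoperative), duration of ICU stay, and lowest systolic blood pressure". For that group, "These outcomes will be analyzed with adjustments for multiple comparisons using Bonferroni correction". For the rest, "Exploratory outcomes will be reported descriptively and analyzed for hypothesis generation, without corrections for multiple comparisons".

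The section on adjustments and multiple comparisons names the same method again: "To account for multiple comparisons across all secondary endpoints, a Bonferroni correction adjustment, will be applied". For the primary outcome it sets the level: "A two-sided p-value of <0.05 will be considered statistically significant for the primary endpoint". It states no family-wise level for the secondary outcomes.

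Neither place mentions a step-down or other sequential version, so the natural reading is single-step Bonferroni. The only confidence interval the article plans is the one for the primary outcome; no simultaneous intervals are planned for secondary outcomes.

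**The concern.** Single-step Bonferroni tests every outcome at 0.05/m, whatever the other outcomes show. Holm tests the smallest p-value at 0.05/m and, if it is significant, the next at 0.05/(m − 1), and so on up to 0.05. Both keep the family-wise error at or below 0.05 without any assumption about how the outcomes are correlated.

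The trial is small and sized on fluid volume alone. The confirmatory secondary outcomes are its only multiplicity-controlled evidence on perfusion, hypotension and ICU stay. If several of these effects are real, plain Bonferroni can leave some of them non-significant that Holm would declare at the same nominal error level.

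**Working it through.** **Inputs from the protocol article**
- Sample size: "With the power of 80%, a 0.05 two-sided difference, the calculated sample size was 25 patients/group" and "Given a dropout rate of 5%, we will enroll 54 patients". The dropout step reproduces: 25/0.95 = 26.3, rounded up to 27 per group, 2 × 27 = 54. The 25 itself cannot be checked because no SD is given. It concerns the primary outcome only.
- Family size: three named outcomes, or four tests if intraoperative and postoperative lactate count separately.

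**Assumptions, because the article does not give them**
- Family-wise level 0.05, two-sided.
- 25 evaluable patients per arm, a t-test for each outcome, correlation 0.3 between test statistics, and a common effect of 0.8 or 0.5 SD on each truly affected outcome.

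**Step 1: thresholds**
- Bonferroni: 0.05/3 = 0.0167 or 0.05/4 = 0.0125 for every test.
- Holm with m = 4: 0.05/4 = 0.0125, 0.05/3 = 0.0167, 0.05/2 = 0.025, 0.05/1 = 0.05, applied to the ordered p-values and stopping at the first failure.

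Holm's first threshold equals Bonferroni's and the later ones are larger, so anything Bonferroni rejects, Holm rejects. Both methods reject nothing when the smallest p-value exceeds 0.05/m. The chance of at least one rejection is therefore identical.

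**Step 2: power by number of real effects** (simulation, 100,000 replicates, m = 4, 0.8 SD; average power per truly affected outcome)

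| Real effects | Bonferroni | Holm | Gain (points) |
|---|---|---|---|
| 1 of 4 | 59.3% | 59.4% | 0.1 |
| 2 of 4 | 59.5% | 62.1% | 2.6 |
| 3 of 4 | 59.4% | 65.1% | 5.7 |
| 4 of 4 | 59.4% | 69.8% | 10.4 |

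The simulation error of one such proportion is at most √(0.5 × 0.5/100,000) = 0.0016, about 0.16 points, so the first row is effectively no gain. With all four effects real, the chance of confirming all four is 21% under Bonferroni and 45% under Holm.

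- m = 4 at 0.5 SD: gains of 0.1, 1.0, 2.2 and 3.9 points for one, two, three and four real effects.
- m = 4 at 0.3 SD: below 1 point throughout.
- m = 3 at 0.8 SD: gains of 0.2, 3.6 and 8.9 points for one, two and three real effects.

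**Step 3: a wider grid** (200,000 draws of normal test statistics, unadjusted power 30% to 90%, correlation 0 or 0.5)
- m = 4: gains of 0.1 points with one real effect, 0.4 to 2.6 with two, 0.8 to 5.8 with three, 1.3 to 10.8 with all four.
- m = 3: gains of 0.1 to 0.2, 0.8 to 3.7, and 1.7 to 9.2 points.

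**Step 4: family-wise error**
- No real effects: the same for both methods, 0.048 to 0.049 in the wider grid.
- Three real effects of 0.8 SD and one true null: about 1.3% for Bonferroni and 3.1% for Holm. Both are under 5%.

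**The case against.** The strongest reply is that nothing here is wrong. Bonferroni is valid under any dependence, it is pre-specified, it inflates no error rate and biases no estimate. Choosing Holm is a preference that could be urged on any trial using Bonferroni. This stands: the point concerns efficiency only.

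A reader might infer that the plan throws away about 10 points of power on each outcome. The documents do not support that. The figure needs all four outcomes to be truly affected by a large amount. The article gives no effect size, SD or correlation for lactate, ICU stay or lowest systolic pressure. The t-test is itself a simplification, since the statistical analysis section plans a Cox model for ICU stay and a mixed model for repeated ICU lactate.

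A reader might also infer that the power is lost for nothing. That is too strong. When some effects are real and others are not, Bonferroni's actual family-wise error is lower (Step 4): Holm's extra power comes from using error allowance that Bonferroni leaves unspent. Bonferroni also has simple matching simultaneous intervals. The article plans no such intervals for secondary outcomes, so this advantage is not used here, but it is real.

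**Conclusion.** The point holds as a cheap, optional improvement. For testing the confirmatory secondary family, Holm uniformly dominates single-step Bonferroni: it gives the same 0.05 family-wise guarantee under any dependence and never fewer rejections.

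Under the stated assumptions with four tests, the gain per affected outcome runs from about 0 to about 10 points at 0.8 SD, and is about 4 points or less at 0.5 SD. Where in that range the trial falls depends on how many effects are real, which the protocol cannot tell us. The primary analysis and the chance of confirming at least one secondary outcome are unaffected. Keeping Bonferroni would be defensible.

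**What to change.** In the secondary outcomes section and in the section on adjustments and multiple comparisons, replace the Bonferroni wording by: *Holm step-down adjustment at family-wise two-sided 0.05 across the confirmatory secondary outcomes*. Report Holm-adjusted p-values. The same edit should state whether lactate counts as one test or two, and should align the reference to all secondary endpoints in the adjustments section with the confirmatory family, since both places leave exploratory outcomes unadjusted.

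The cost is two changes of wording and no new data; they should be made before unblinding. The article plans SPSS for all analyses; Holm needs only the ordered p-values and a few multiplications. If intervals for these outcomes are wanted, Bonferroni-width intervals can be shown as descriptive companions, with a note that they may not match the Holm decisions exactly.

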### Data collections and data management

The non-endpoint data include patient characteristics and details regarding the operation and anesthesia. Types and dosages of anesthetic and opioids administered during surgical procedures, hemodynamic data, mannitol administration, use of inotropic or vasopressor agents, volume of blood transfusion, estimated blood loss, urine output, and duration of surgery will be recorded in the case record form (CRF). Two independent anesthesiologists, blinded to the group allocation, will check the data, patient safety, the accuracy and safety of data, and the study progression once a month.

### Sample size calculation

The primary outcome is the intraoperative fluid volume administered. The calculation of sample size utilized data from the research conducted by Janani Gopal et al [18]. The average fluid volume administration of patients in the CVP and PPV groups were 4,300 and 3,500 ml, respectively. In another study, the groups that used CVP guidance and those that used PPV guidance had a mean intraoperative fluid volume difference of 556 milliliters [25]. With the power of 80%, a 0.05 two-sided difference, the calculated sample size was 25 patients/group. Given a dropout rate of 5%, we will enroll 54 patients. The website clincalc.com is used to calculate the sample size. We anticipate a minimal drop-out and low loss to follow-up rate, as the study is conducted while the patient is under general anesthetic during surgery. Additionally, post-surgery, all patients will be admitted to the neurosurgical ICU, where we can gather data regarding the duration of their ICU stay.

### Statistical analysis

Baseline variables will be summarized using descriptive statistics (mean, standard deviation, median, interquartile range, or frequency and percentage, as appropriate). A modified intention-to-treat (ITT) principle will be used for all analyses. Data distribution will be assessed using the Kolmogorov-Smirnov test. Comparisons between groups (PPV vs. CVP) will be conducted as follows:

#### Primary outcome.

The primary outcome, the volume of intravenous fluid administered at multiple time points (t2 to t5), will be analyzed using a linear mixed-effects model (LMM) to account for repeated measures. Group (PPV vs. CVP), time (t2–t5), and interaction between group and time will be included as fixed effects, with a random intercept to account for within-patient correlation. Covariates will also be incorporated as fixed effects to adjust for potential baseline imbalances. For non-normal data, the generalized estimating equations (GEE) will be used.

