### Outcomes

#### Primary outcome.

The primary outcome is the mean volume of intravenous fluids administered intraoperatively in the PPV group vs in the CVP group. The data will be represented in mean difference, 95% confidence interval, and p-value.

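### The primary outcome is defined and sized as one intraoperative volume per patient but analysed as volumes at t2 to t5, without saying whether these are interval or cumulative or which model effect is the primary test

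*Protocol article*

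**What the plan says.** The Outcomes section states: "The primary outcome is the mean volume of intravenous fluids administered intraoperatively in the PPV group vs in the CVP group". It promises a single summary: "The data will be represented in mean difference, 95% confidence interval, and p-value". The Sample size calculation section repeats that "The primary outcome is the intraoperative fluid volume administered" and works from group means of 4,300 and 3,500 ml and, from a second study, a difference of 556 ml. The Abstract speaks of at least 500 ml. None of these uses a repeated-measures input.

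Under Statistical analysis, Primary outcome, the same outcome becomes a repeated measurement: "the volume of intravenous fluid administered at multiple time points (t2 to t5), will be analyzed using a linear mixed-effects model (LMM"). The model terms are listed next: "Group (PPV vs. CVP), time (t2–t5), and interaction between group and time will be included as fixed effects". For the correlation between a patient's own values, a random intercept is the only term given. Unnamed covariates are added, and GEE is the fallback for non-normal data. The section Adjustments and multiple comparisons then says: "A two-sided p-value of <0.05 will be considered statistically significant for the primary endpoint". No section states which term or contrast of the model this p-value belongs to. The time points may be defined in Fig 1, which is not available here.

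**The concern.** A model with four time points and a group-by-time interaction offers several quantities that could be called the group difference: the coefficient printed for group, the group effect averaged over time, the difference at t5, and the interaction test. They answer different questions. Whether any of them is the difference in total volume depends on how the volumes are coded, and the plan does not say.

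This is the trial's only primary endpoint, with 54 patients. If coding and contrast are settled after the data are seen, the reported number may not be the quantity the trial was sized for, and its confidence interval may be too narrow.

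**Working it through.** **1. What the sample size assumes.** For a two-group comparison of one value per patient, n per group = 2 (1.96 + 0.8416)² SD² / Δ². No SD is given, so 25 per group cannot be confirmed directly. Solving for the SD, SD = Δ × √(25/2) / 2.8016:
- Δ = 500 ml: 500 × 3.5355 / 2.8016 = 631 ml
- Δ = 556 ml: 702 ml
- Δ = 800 ml (4,300 − 3,500): 1,010 ml

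Dropout: 25 / 0.95 = 26.3, so 27 per arm and 54 in all, which agrees with the plan. The inputs fit a single total per patient.

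**2. Interval volumes that cover the whole operation.** Let dⱼ be the group difference in interval j. The total difference is d₂ + d₃ + d₄ + d₅, and the time-averaged group effect is that sum divided by 4. A total difference of 500 ml appears as 125 ml. This is only a change of scale. In a generated balanced data set, the mixed-model statistic for the averaged effect was 3.658 and the t statistic on the totals was 3.658. In null simulations with 25 per arm, the averaged effect rejected in 4.8 to 5.2% of trials under every covariance tried.

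**3. Cumulative volumes: the averaged effect.** For a true total difference of 500 ml:
- even accrual: (125 + 250 + 375 + 500) / 4 = 312.5 ml
- all in the last interval: (0 + 0 + 0 + 500) / 4 = 125 ml

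Simulated power with 25 per group and an SD of the total of 631 ml was 71 to 75% in the first case and about 18% in the second. A t-test on the total gave about 78% in both (80% by the normal approximation). The averaged effect keeps its 5% level here too, but it estimates something else.

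**4. Cumulative volumes: the t5 contrast.** This contrast is the total if t5 is the end of surgery. A random intercept with independent, equal-variance residuals forces one variance on all four times. In balanced data the fitted value is the average of the four true variances. Take increments of unit variance:
- *Independent increments.* Variances 1, 2, 3, 4; average 2.5. The true standard error at t5 is √(4 / 2.5) = 1.265 times the model's. The effective critical value is 1.96 / 1.265 = 1.549, so the two-sided error is 12.1%.
- *Increments correlated 0.3.* Var(k) = k + 0.3 k(k − 1), which gives 1, 2.6, 4.8, 7.6; average 4.0. The ratio is √(7.6 / 4.0) = 1.378 and the critical value 1.422, so the two-sided error is 15.5%.

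Simulation gave 12.1% and 15.4% for these two cases, and 12 to 15% with gamma-distributed increments and 27 per arm. A plain t-test at t5 gave 5.1%.

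**5. The interaction test.** It rejected in 5.0% of null trials with interval volumes under compound symmetry and in 7.1 to 8.8% with cumulative volumes.

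**6. The printed group coefficient.** With the interaction in the model and reference coding, this coefficient is the group difference at the reference time only. In the data set of step 2 it was about 131 ml, the difference at t2 alone, while the difference in totals was 447 ml.

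**The case against.** The best defence is that the model can deliver the promised comparison. With complete interval volumes, the averaged group effect is exactly the test of the total, and it holds its level even when the random-intercept structure is wrong. That stands. A reader might infer from the mismatch that the mixed model contains no valid test of the total, or that it is anti-conservative throughout. Steps 2 and 3 show that neither is so.

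A reader might also infer that significance on any of the group, interaction or time-specific tests would count as success, and compute an error rate for that. The document states no such rule. Its promise of one mean difference with a confidence interval does not fit an interaction test, so such a rate would describe selective reporting and not the written plan.

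It can also be said that time-point definitions, coding and contrasts belong in a figure or a separate analysis plan. In part that is fair: Fig 1 may define t2 to t5, and the residual covariance is not stated. But the article does set out the primary model, its fixed effects, its random effect and the significance level, and what it sets out departs from its own definition and sizing of the outcome. Labels for the time points would not by themselves name the primary test.

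**Conclusion.** The point holds as a mismatch between the endpoint as defined and sized and the primary analysis as written. One reading, complete interval volumes with the averaged group effect as the test, gives a valid analysis of the total. Nothing in the text selects it. Under cumulative coding the averaged effect is a different quantity, and the contrast that equals the total has a type I error of about 12 to 15% instead of 5%.

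That figure is conditional. It rests on cumulative volumes, on t5 being the tested contrast, on a random intercept as the only covariance term, and on the assumed increment structures, since the document gives none. The power figures rest on an SD of 631 ml, back-solved for a 500 ml difference.

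**What to change.** Make the primary analysis a linear model (ANCOVA) of each patient's total intraoperative intravenous fluid volume on group, with baseline covariates named in advance. Body weight is an obvious one, because the Fluid management protocol section makes maintenance fluid weight-based. Report the adjusted mean difference, 95% confidence interval and p-value. Keep the t2 to t5 model as a supportive description of timing, using interval volumes or an unstructured covariance, with no claim attached to its p-values.

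An equivalent repair inside the mixed model is to state that the volumes are per interval and cover the whole operation, and to name the sum of the four interval group differences as the only primary test.

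The cost is one paragraph. The total is the sum of volumes already recorded. In simulation the comparison of totals held 5.0 to 5.2% type I error, and 25 per group needs no change on this account.

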#### Secondary outcomes.

***Intraoperative data:*** Continuous variables (e.g., lowest systolic BP, blood loss, urine output) will be analyzed using an independent sample t-test or Mann-Whitney U test, as appropriate. Covariates will be adjusted using an analysis of covariance (ANCOVA). Categorical variables (e.g., vasopressor use, incidence of extubation) will be compared using the Chi-square test or Fisher’s exact test. For ordinal variables (e.g., brain relaxation score), a Mann-Whitney U test will be used.

***Postoperative data:*** For time-dependent outcomes (e.g., duration of mechanical ventilation, ICU length of stay), a Cox proportional hazards model will be used to estimate hazard ratios between groups (PPV vs. CVP), including baseline covariates to control for potential confounding. Kaplan-Meier survival analysis will be performed for graphical representation. Continuous variables (e.g., serum lactate levels, BUN/Cr values) will be compared using a t-test or Mann-Whitney U test, while categorical variables (e.g., chest X-ray abnormalities) will be compared using Chi-square or Fisher’s exact test. For repeated measures within the ICU (e.g., serum lactate levels over time), a linear mixed-effects model (LMM) will be applied.

### Adjustments and multiple comparisons

To adjust for potential baseline covariate imbalances, specific analyses including ANCOVA, Cox proportional-hazards model, or LMM) will be used. To account for multiple comparisons across all secondary endpoints, a Bonferroni correction adjustment, will be applied.

A two-sided p-value of <0.05 will be considered statistically significant for the primary endpoint. The exploratory secondary analyses will report unadjusted p-values to guide future research. All statistical analyses will be performed using SPSS software by an expert statistician.

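### One sentence extends the Bonferroni correction to every secondary endpoint, against two others that leave exploratory outcomes unadjusted; the threshold for the confirmatory secondaries must be stated once

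*Protocol article*

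**What the plan says.** In the Secondary outcomes subsection under Outcomes, the secondaries are split into two classes. The first class is named: "Confirmatory secondary outcomes include serum lactate levels (intraoperative and postoperative), duration of ICU stay, and lowest systolic blood pressure". The rule for it follows at once: "These outcomes will be analyzed with adjustments for multiple comparisons using Bonferroni correction". All remaining secondaries form the second class, with its own rule: "Exploratory outcomes will be reported descriptively and analyzed for hypothesis generation, without corrections for multiple comparisons".

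The section Adjustments and multiple comparisons returns to the subject. Its first paragraph ends: "To account for multiple comparisons across all secondary endpoints, a Bonferroni correction adjustment, will be applied". Its second paragraph sets the primary threshold, "A two-sided p-value of <0.05 will be considered statistically significant for the primary endpoint", and then adds: "The exploratory secondary analyses will report unadjusted p-values to guide future research".

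No place in the article gives the number of comparisons in the family, a family-wise level for the secondaries, or the resulting per-test threshold.

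**The concern.** A Bonferroni threshold is fixed entirely by the number of tests in the family. The article describes that family in two ways: the confirmatory secondaries only, or all secondaries. The broad version also clashes with the sentence in the next paragraph, because the exploratory secondaries cannot be both corrected and unadjusted.

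The outcomes at stake are the ones the sponsor itself calls confirmatory: lactate, ICU stay and lowest systolic pressure. A confirmatory label calls for one threshold, fixed in advance. With two published wordings, a result between the two thresholds could be claimed or not claimed by citing either, and a reader could not tell whether the choice preceded the p-values. Blinding the statistician to group labels does not settle this, because the choice of divisor does not depend on knowing which group is which.

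**Working it through.** The article gives no adjusted threshold to reproduce, so the figures below are derived from its lists.

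**Inputs from the article**
- Intraoperative secondaries: 7 numbered items, the last being "7) the incidence of extubation in the operating theater (no. and" %).
- Postoperative secondaries: 4 numbered items. Item 3 bundles two or three measures: "3) chest X-ray, and BUN/Cr values and (4) The duration of the" stay.
- Confirmatory outcomes: lowest systolic pressure (intraoperative item 1), intraoperative lactate (item 5), postoperative lactate (postoperative item 2) and ICU stay (item 4). That makes 4 of the numbered items, or 3 if lactate is counted once.
- Sample size: 54 patients, hence 27 per group.

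**Assumptions, not in the article**
- A family-wise two-sided level of 0.05 for the secondaries.
- For the power illustration only: a standardized effect d = 0.8 and a two-sample t-test with all 27 per group analysed.

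**Step 1: thresholds, 0.05/k**

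| Family | k | Per-test threshold |
|---|---|---|
| Confirmatory, lactate counted once | 3 | 0.0167 |
| Confirmatory, as numbered | 4 | 0.0125 |
| All secondaries, as numbered (7 + 4) | 11 | 0.0045 |
| All, chest X-ray split from BUN/Cr | 12 | 0.0042 |
| All, BUN and Cr split as well | 13 | 0.0038 |

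A p-value of 0.008 is below 0.0125 and above 0.0045, so it is significant under one rule and not under the other.

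**Step 2: error rate actually spent on the four confirmatory tests** (taken as independent), 1 − (1 − a)^4
- a = 0.0125: 1 − 0.9875^4 = 0.049.
- a = 0.00455: 1 − 0.99545^4 = 0.018.

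The broad divisor therefore uses well under half of the assumed 0.05 on the outcomes meant for confirmation.

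**Step 3: illustrative power for one confirmatory outcome**
- Noncentrality = d × √(n/2) = 0.8 × √13.5 = 2.94, with 52 degrees of freedom.
- a = 0.0125: critical t = 2.588, power 63.8%.
- a = 0.00455: critical t = 2.966, power 49.5%.
- Difference: about 14 percentage points.

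**Step 4: Bonferroni against Holm, same illustration.** With four endpoints, each with d = 0.8 and correlated at 0.3, the average per-endpoint power by simulation (100,000 runs) is about 64% with Bonferroni and 74% with Holm. The Bonferroni figure must equal the single-endpoint value in Step 3 whatever the correlation, and it does.

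**The case against.** The strongest reply is that the rule is less open than a side-by-side reading suggests. The Secondary outcomes section is the more specific text: it names the confirmatory outcomes, attaches the correction to them and excludes the rest. The later sentence on unadjusted exploratory p-values agrees with it. Two statements point one way, and a single loosely worded sentence is the outlier. This stands. A reader might infer that the two rules have equal standing and that the threshold is a coin-toss; the article does not support that, and the confirmatory-only rule is the likelier intent. It does not remove the defect, because the outlier sits in the section that governs multiplicity. It can even be squared with unadjusted exploratory p-values, by dividing by 11 and judging only the confirmatory four at 0.0045.

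A second reply is that the divisor and threshold are details for an analysis plan that is not shown. Their absence alone would indeed be no finding. The finding is that the rule the article does state is stated in incompatible ways.

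A third reply concerns the figures. The thresholds depend on an assumed family-wise 0.05 and on how outcomes are counted. The effect of 0.8 has no source in the article. A t-test is also not the planned analysis for every confirmatory outcome: ICU stay is to be analysed by a Cox model and repeated ICU lactate by a mixed model. All of this stands, so the power figures are an illustration and not an estimate for this trial.

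Finally, a reader might infer that the sponsor means to choose the divisor after seeing results. Nothing in the article shows that; the wording merely leaves room for it.

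**Conclusion.** The contradiction is real and lies in the current text. Under an assumed family-wise 0.05, the confirmatory secondaries face 0.0125 (0.0167 with lactate counted once) under the Secondary outcomes section, and about 0.0045 (down to 0.0038, depending on the count) under the literal sentence in the adjustments section. Only confirmatory results with p-values between those limits change status. In the illustration, the stricter rule costs about 14 points of power.

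It would go too far to conclude that the trial's main inference is compromised. The primary endpoint keeps its own two-sided 0.05, and sample size, data collection and conduct are unaffected. Nor is Bonferroni itself at fault; it is valid for either family. This is a point that should be fixed, not one on which the trial depends.

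**What to change.** Before any group comparison is run, replace the sentence in Adjustments and multiple comparisons with wording such as:

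> *Bonferroni correction is applied across the four confirmatory secondary tests (intraoperative lactate, postoperative lactate, ICU stay, lowest systolic pressure; family-wise two-sided alpha 0.05, threshold 0.0125 each). All other secondary outcomes are exploratory and unadjusted.*

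Name one group comparison in advance for each lactate outcome. Intraoperative lactate is measured hourly and ICU lactate repeatedly, and testing each time point would enlarge the family beyond four.

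Optionally, use Holm's step-down procedure in place of Bonferroni. It gives the same family-wise control, is never less powerful, and gains about 10 points of average power in the illustration above. It is not needed to cure the contradiction.

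The cost is one replaced sentence plus the definition of the two lactate comparisons, with no extra data or patients.
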